### Participant timeline

#### Visit 1

Potential trial candidates will attend their first visit for registration and consent by the PI or delegate. If required, further tests to exclude diagnoses other than IBS-D will be arranged. These include a SeHCAT scan, serum C4 level, or a 1-week trial of a bile-acid binding agent to assess for bile acid malabsorption (unless done within the last 5 years), and colonoscopy (unless done within 2 years, or 5 years if they also currently have normal calprotectin) to assess for microscopic colitis. Baseline serum blood tests, vital signs, demographics (date of birth, gender, ethnicity, and smoking history) and an ECG will be obtained. Current medications will be reviewed, and those unable to discontinue drugs likely to alter bowel habit will be unable to enter the trial. Patients on QT-prolonging drugs and cardiotoxic drugs will be reviewed by the PI for suitability for the trial, as ondansetron may increase the risk of QT prolongation and arrhythmias. Eligible and consenting patients are registered and allocated a unique trial ID and data collected will be link anonymised.

All patients will be asked to complete a 2-week daily diary recording stool frequency, the consistency of each stool (using the BSFS), worst abdominal pain (on a scale of 0–100), worst bowel movement urgency (on a scale 0–100), and if they have used loperamide that day. In addition, patients have the option to be sent two automated text messages each day. The first will ask the patient if they have passed a stool of consistency 6 or 7 on the BSFS. They will need to reply with either a yes or no. The second text message will ask what their worst abdominal pain score was that day. The patient must respond with a number from a scale of 0–100 (where 0 is no pain and 100 is the worst imaginable pain).

#### Visit 2

The patient will return 2 weeks later to confirm eligibility. The diary will confirm they have had stool consistency BSFS 6–7 for more than 2 days a week and do not have only BSFS 7 for 7 days per week, and a weekly average worst pain score ≥ 30. Patients who consent to the whole gut transit study will be dispensed Transit-Pellet capsules containing markers, and the abdominal x-ray appointment will be confirmed for the morning of visit 3. Patients will take the Transit-Pellet capsules for 6 days prior to visit 3. Patients who have consented to one or both mechanistic studies will have appointments arranged for baseline assessment prior to visit 3.

#### Visit 3

On visit 3, patients will undergo a pregnancy test if applicable, whole gut transit assessment by abdominal x-ray (if they have consented), rigid sigmoidoscopy (if they have consented), completion of baseline questionnaire booklet (including IBS-SSS, SF-LDQ, HADS, PHQ-12, and IBS-QOL questionnaires), and collection of stool, whole blood, and serum samples (if they have consented). Patients will then be randomised and given a 6-week patient diary and the trial medication in accordance with their blinded randomisation allocation. Patients will be asked to record the following on a daily basis: stool frequency, consistency of each stool, worst abdominal pain experienced that day, worst bowel movement urgency, number of trial medication capsules taken, and whether they have used loperamide that day. Every week the diary will ask whether they feel that they have had satisfactory relief from their IBS symptoms that week. If they agree, the patient will continue to receive two text messages each day for the next 6 weeks, asking if they have passed a stool of a consistency of 6 or 7 that day, and what their worst abdominal pain was that day.

During the first 2 weeks patients will be contacted every 2 days by the local site team to discuss bowel habit. The dose of ondansetron or placebo will then be titrated as required. Additional guidance on dose titration will be given to each trial site in a standard operating procedure, and to the patient in a dose titration instruction leaflet. A check for serious adverse events (SAEs) will be performed during each telephone call. The steady dose to be taken forward for the remainder of the trial will be confirmed in week 2, although this may be altered during the 12 weeks if required, to avoid constipation.

#### Visit 4

Patients will return for their fourth visit at 6 weeks of the trial treatment period. Diaries will be collected, and the investigator will ask whether any reportable AEs have occurred since the last visit. A pregnancy test will be taken and concurrent medications will be reviewed to ensure these do not interfere with the trial medication. A further 6-week patient diary, trial medication, and Transit-Pellet capsules (for use 6 days prior to visit 5) will be dispensed. Patients who have consented to mechanistic studies will have appointments confirmed and these will take place between 8 and 11 weeks of treatment. Daily text messages will be sent for a further 6 weeks to those patients who agree.

#### Visit 5

Patients will return for visit 5 after 12 weeks on the trial medication. A pregnancy test will be taken, concurrent medication will be reviewed to ensure that these do not interfere with the trial medication, and the investigator will ask whether any reportable AEs have occurred since the last visit. Unused medication and completed patient diaries will be collected. The abdominal x-ray to assess whole gut transit will be performed in consenting patients. Serum and stool samples will be collected from consenting patients, and all patients will complete the 12-week questionnaire booklet, including the IBS-SSS, SF-LDQ, HADS, and IBS-QOL questionnaires. Patients will be issued with a follow up diary and will continue to respond to text messages for a further 4 weeks.

#### Visit 6

Patients will then return for the sixth and final visit, where the diary will be collected and the investigator will ask whether any reportable AEs have occurred since the last visit.

### Sample size

TRITON plans to recruit 400 patients from up to 24 sites across England and Scotland. This will provide 90% power at 5% significance to detect a 15% absolute difference between the randomised groups in the proportion of patients achieving the FDA-recommended [28] endpoint of a weekly response for pain intensity and stool consistency for at least 6 weeks of the 12-week treatment period. This difference (15%) is considered to represent the minimum clinically important difference. We have assumed a placebo response rate of 17%, as recently reported using this endpoint and allowed for a 15% attrition rate.

#### Whole gut transit

Our previous study using the same radio-opaque marker technique as we propose to use showed ondansetron increased whole gut transit time by a mean (95% CI) of 10 (6–14) h. Using 200 patients per group gives 90% power to detect a change of 0.7 h. The larger numbers will also give us the power to test correlation with other endpoints.

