### Investigational agent

Ondansetron is a potent, highly selective 5HT_3_RA, which blocks 5HT_3_ receptors in the gastro-intestinal tract and in the central nervous system. Ondansetron is currently licenced for use in adults and children for the management of nausea and vomiting induced by cytotoxic chemotherapy and radiotherapy, and for the prevention and treatment of post-operative nausea and vomiting. Constipation is an unintended side effect of ondansetron, which was first shown to slow colonic transit 30 years ago [18–20]. In our pilot study, 120 patients were recruited to a randomised double-blind, placebo-controlled, cross-over trial of ondansetron treatment for IBS-D. Patients were randomised to receive ondansetron (2 mg per day up to 8 mg t.d.s) followed by placebo or placebo followed by ondansetron. Patients began on drug A for a period of 5 weeks, then underwent a washout period of 2–3 weeks, and then commenced drug B for 5 weeks. The primary outcome measure for the study was the difference in average stool consistency in the last 2 weeks of treatment of ondansetron versus placebo, and this showed a highly significant improvement with active treatment. We also showed significant benefits for both urgency and stool frequency, with associated slowing of whole gut transit. Despite having limitations, the results of this pilot study were very encouraging, supporting our clinical experience of the benefits of ondansetron.

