### Trial design

TRITON is a multi-site, parallel group, randomised, double-blind, placebo-controlled trial with embedded mechanistic studies within selected sites. Our aim is to determine the superiority of ondansetron compared with placebo. In total, 400 patients with IBS-D will be randomised 1:1 to receive either ondansetron or placebo. Both treatments will be administered in oral doses of between 4 mg every third day and 24 mg daily for 12 weeks. Dose titration will be undertaken in the first 2 weeks of the trial to avoid constipation, which at a standard dose occurs in one quarter of patients. The primary outcome will be assessed over the 12 weeks post randomisation. Secondary and safety outcomes will be measured up to 16 weeks following randomisation. See Fig. 1 for an overview of the trial procedures. The Standard Protocol Items: Recommendations for Interventional Trials (SPIRIT) checklist is provided as an Additional file 1.

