### Data analysis

#### General considerations

All hypothesis tests will be two-sided with a 5% significance level. Methods to handle missing data are described for each analysis. Analysis and reporting will be in line with Consolidated Standards of Reporting Trials (CONSORT) [30]. As TRITON is a double-blind trial, the trial statistician will be blinded to treatment group allocation throughout the trial, until the database has been locked and downloaded for final analysis. Only the safety statistician, supervising trial statistician, back-up safety statistician, and authorised unblinded individuals at the CTRU will have access to unblinded treatment group allocation prior to final analysis.

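### The claimed 90% power to detect a 0.7 h change in whole gut transit is incompatible with the confidence interval quoted beside it

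*Protocol article*

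**What the plan says.** The Whole gut transit paragraph of the Sample size section makes two linked statements. It first says that an earlier study with the same marker technique "showed ondansetron increased whole gut transit time by a mean (95% CI) of 10 (6–14) h". It then says: "Using 200 patients per group gives 90% power to detect a change of 0.7 h". No standard deviation is given there or elsewhere for transit time or its change.

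The other inputs are spread through the article:

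- **Test (General considerations):** "All hypothesis tests will be two-sided with a 5% significance level".
- **Allocation (Trial design):** "400 patients with IBS-D will be randomised 1:1 to receive either ondansetron or placebo".
- **Comparison (Mechanistic studies, under Data analysis):** the two groups are compared on change in transit time by linear regression.
- **Earlier study (Investigational agent):** "120 patients were recruited to a randomised double-blind, placebo-controlled, cross-over trial". The number of those patients with paired transit data is not stated.
- **Who contributes transit data (Participant timeline, Visit 2):** "Patients who consent to the whole gut transit study will be dispensed Transit-Pellet capsules containing markers". Transit is thus measured only in those who agree to it, although Mechanistic outcome measures plans it for 400.
- **Losses (Sample size, for the primary endpoint):** the calculation "allowed for a 15% attrition rate".

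**The concern.** A confidence interval for a mean fixes its standard error. The standard deviation of individual values is larger by the square root of the number of patients. An interval that runs 4 h either side of the mean, from a study of any ordinary size, implies that individual changes vary by many hours. A trial with 200 per group could not then resolve a difference of 0.7 h, which is 42 minutes.

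What is at stake is the sensitivity claimed for a mechanistic endpoint. Slower transit is the article's proposed route to lower faecal protease and bile acid. A reader who accepts 0.7 h could take a non-significant transit result as evidence against any effect of an hour or more, when the trial could miss effects of several hours.

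**Working it through.** **Inputs.** Earlier effect 10 h, 95% CI 6 to 14 h; 200 per group; 90% power (all from Whole gut transit). Two-sided 5% (General considerations). 1:1 allocation (Trial design).

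**Formula.** Detectable difference = (1.960 + 1.282) × SD × √(2/n) = 3.2415 × SD × √(2/n). With n = 200, √(2/200) = 0.1.

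**Step 1: standard error from the interval.** SE = (14 − 6)/(2 × 1.96) = 2.04 h.

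**Step 2: SD that 0.7 h requires.** SD = 0.7/(3.2415 × 0.1) = 2.16 h by the normal approximation, or 2.15 h with the t distribution.

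**Step 3: consistency with the interval.** If SE = SD/√m, then m = (2.16/2.04)² ≈ 1.1 patients. Two more favourable readings do not help:

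- If the relevant SD were the paired-difference SD divided by √2, m would be about 2 × 1.12 = 2.2 patients.
- If the earlier interval came from two parallel groups, m would be about 2.2 per group.

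An SD of 2.16 h would also make the 10 h effect about 10/2.16 = 4.6 standard deviations.

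**Step 4: what reproduces 0.7 h.** With 2.04 h entered as the SD, 3.2415 × 2.04 × 0.1 = 0.66 h, which rounds to 0.7 h. At 170 per group the same substitution gives 0.72 h. A one-sample formula gives 0.47 h (n = 200), and a one-sided two-sample test gives 0.60 h.

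**Step 5: detectable difference with SD = 2.04 × √m.** Here m is the number with paired transit data in the earlier study. It is not given; 20 to 120 is assumed, the upper end being everyone recruited to the pilot. The SD of the paired difference is assumed to carry over to the change from baseline in the new trial. The 170 column is 200 × 0.85, applying the 15% attrition.

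| m (assumed) | SD of change, h | Detectable, 200 per group, h | Ratio to 0.7 h | Detectable, 170 per group, h | Power for 0.7 h, 200 per group |
|---|---|---|---|---|---|
| 20 | 9.1 | 3.0 | 4.2 | 3.2 | 12% |
| 40 | 12.9 | 4.2 | 6.0 | 4.5 | 8% |
| 60 | 15.8 | 5.1 | 7.3 | 5.6 | 6.5% |
| 80 | 18.3 | 5.9 | 8.5 | 6.4 | 6% |
| 100 | 20.4 | 6.6 | 9.5 | 7.2 | 5% |
| 120 | 22.4 | 7.3 | 10.4 | 7.9 | 5% |

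The power column counts only rejections in the direction of the true effect. For 90% power at 0.7 h, about 3,600 (m = 20) to 21,400 (m = 120) patients per group would be needed.

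The most optimistic variant divides the SD by √2. At m = 20 it gives SD 6.5 h, a detectable difference of 2.1 h (3 times 0.7 h) and 19% power for 0.7 h.

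**Step 6: power for the earlier effect.** With the largest SD (22.4 h) and 200 per group, 10/(22.4 × 0.1) = 4.47, and 4.47 − 1.96 = 2.51 gives 99.4%. At 170 per group, 10/(22.4 × 0.1085) ≈ 4.12, and 4.12 − 1.96 = 2.16 gives about 98%.

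**The case against.** The figure itself has no defence: baseline adjustment, a paired formula or a one-sided test does not recover it. The case on the other side concerns how much follows from the error, and most of it stands.

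- **Cause.** A reader might infer that the sponsor certainly used the standard error as the standard deviation. The article does not say so. The match at 0.66 h is close but not unique. With about 112 paired patients, SD = 2.04 × √112 = 21.6 h and the detectable difference is 7.0 h, so a misplaced decimal point would also print 0.7.
- **Size.** A reader might take a fixed multiple, such as 4- to 10-fold, as established. It depends on the assumed 20 to 120 paired patients. Treating the unnamed earlier study as the 120-patient pilot is also an assumption. The incompatibility in Step 3 needs neither.
- **Adequacy.** A reader might infer that the transit comparison is underpowered. It is not for an effect like the earlier one. The 400 patients are set by the primary endpoint, and power for 10 h remains at or above 98%.
- **Correlations.** The same paragraph says that the larger numbers give power to test correlations. That depends on the number of patients and the size of the correlation, so the 0.7 h error does not undermine it.
- **Interpretation.** The article sets no equivalence margin or decision threshold at 0.7 h, and the reported confidence interval will show the precision achieved. Misreading a null result is therefore a risk, not a planned inference.
- **Consent and attrition.** The attrition allowance is stated for the primary endpoint, and going from 200 to 170 per group raises the detectable difference by only about 8%. Expected transit uptake may be given in the full protocol.

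**Conclusion.** Wrong as written. The 90% power claimed for 0.7 h contradicts the interval printed next to it, because it needs an SD of change of about 2.15 h against a standard error of 2.04 h, which means an earlier study of about one patient. This follows from the article's own figures, whatever the size of the earlier study.

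How far the figure is out is conditional. If 20 to 120 patients had paired transit data, and the paired SD carries over to the new trial, the 90%-power detectable difference is about 3 to 7 h at 200 per group and 3.2 to 7.9 h at 170 per group. Power for 0.7 h is about 5 to 12%, not 90%.

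The error is confined to one stated figure for a mechanistic endpoint. It does not touch the primary endpoint or the trial's size.

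**What to change.** Delete the 0.7 h figure. Recover the SD of individual change from the sponsor's own earlier data, either directly or as the standard error times the square root of the number with paired transit data, and state both that SD and that number. Then restate the difference detectable with 90% power, using the number per group expected to consent to and complete both transit assessments. No value should be written in until the earlier data have been consulted, since the range above rests on an assumed number of patients.

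The cost is a change of wording. The stated sensitivity becomes less favourable, from under an hour to probably several hours. No extra patients and no change of design or analysis are needed.

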#### High-resolution left-sided colonic manometry

Previous studies with the closely related 5HT_3_RA alosetron showed an increase in motility index compared with placebo, with a mean (standard deviation (SD)) of 1.0 (1.2) [29], indicating we would have 80% power to detect a standardised effect size of 1 with 17 patients. We will aim for 20 patients on each treatment to allow for dropouts i.e. 40 each undergoing two studies, a total of 80 high-resolution manometry (HRM) studies.

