#### Mechanistic outcome measures

The trial will evaluate the possible mechanisms underlying any changes in the primary and secondary endpoints. The effect of ondansetron on whole gut transit will be measured at baseline and 12 weeks (*n* = 400), using radio-opaque markers and an abdominal x-ray as previously described [27]. High-resolution manometry will be performed at baseline and after 8–11 weeks of treatment at two centres (*n* = 40) to assess whether ondansetron decreases the number of high-amplitude propagating contractions and increases the percentage time occupied by cyclical retrograde propagated contractions [11]. Barostat assessment will be performed at baseline and after 8–11 weeks of treatment at four centres (*n* = 80, some of whom may also undergo manometry), in order to assess if ondansetron increases rectal compliance and decreases sensitivity (manifested as increased pressure thresholds for pain and urgency). Serum will be sampled to genotype patients for polymorphisms in the *TPH1* gene (*n* = 400), and correlation tested between these and the mucosal 5HT and TPH-1 mRNA obtained from high-rectal biopsies (*n* = 80), final ondansetron dose, and responder status, to see whether this predicts sensitivity and/or response to ondansetron. Finally, stool sample analysis (*n* = 400) will be used to assess whether ondansetron reduces total faecal bile acid and tryptase concentrations, and correlation will be tested between these and any changes in urgency.

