### Randomisation

Randomisation will be performed on a 1:1 basis to receive either ondansetron or placebo, and each patient will be allocated three bottles of trial medication, each with a unique IMP kit code. Minimisation will be used, in order to ensure treatment groups are well-balanced. The stratification factors are registering site and whether the patient has undergone mechanistic assessments.

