#### Mechanistic studies

Mechanistic studies will be analysed blinded to the intervention allocation, by the site research fellow under supervision of the Chief investigator and local supervising PIs. The differences between treatment groups in changes in whole gut transit times, colonic motility measures (percent time of cyclical retrograde contractions and high-amplitude propagating contraction (HAPC) frequency), rectal compliance, and thresholds for urgency and pain measured using the barostat, faecal bile acid concentrations, and faecal tryptase will each be assessed by linear regression models. In addition, exploratory mediator analyses will explore whether treatment effects, in terms of changes in urgency or pain, are mediated through changes in faecal bile acids or protease. Exploratory subgroup analysis (tests of interactions) will be performed to investigate the effect of the presence of each specified single nucleotide polymorphism allele on response to treatment, using logistic regression with addition of an interaction term for the allele and treatment.

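### The effect cited for the manometry sub-study (1.0, SD 1.2) is a standardised 0.83, so it does not support the target of 1 on which the 80% power rests

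*Protocol article*

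**What the plan says.** Under Sample size, the subsection on high-resolution left-sided colonic manometry cites an increase in motility index with alosetron over placebo, "with a mean (standard deviation (SD)) of 1.0 (1.2) [29], indicating we would have 80% power to detect a standardised effect size of 1". The sample is 17 patients, and the plan then adds: "We will aim for 20 patients on each treatment to allow for dropouts". That makes 40 patients, each studied twice.

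The motility index is named only in that subsection. Under Mechanistic outcome measures, manometry is to assess whether ondansetron "decreases the number of high-amplitude propagating contractions and increases the percentage time occupied by cyclical retrograde propagated contractions". Under Mechanistic studies, the measures to be compared between groups are again "percent time of cyclical retrograde contractions and high-amplitude propagating contraction (HAPC) frequency".

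**The concern.** The wording offers the alosetron result as the reason why a standardised effect of 1 can be detected. A standardised effect is the mean difference divided by the SD, and 1.0 divided by 1.2 is not 1. It looks as though the raw mean was carried over without the division. No other reason is given for choosing 1.

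What is at stake is how the sub-study's power is understood. A reader would take it that an effect of the size seen with alosetron has an 80% chance of being detected. On the cited figures the chance is lower, even if nobody drops out.

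**Working it through.** **Inputs**

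- Cited effect: mean 1.0, SD 1.2 (manometry subsection of Sample size).
- Stated result: "80% power to detect a standardised effect size of 1 with 17 patients" (same subsection).
- Planned number: 20 per treatment (same subsection).
- Test: "All hypothesis tests will be two-sided with a 5% significance level" (General considerations).
- Allocation: "Randomisation will be performed on a 1:1 basis to receive either ondansetron or placebo" (Randomisation).
- Comparison: changes compared between the two groups (Mechanistic studies).

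**Method.** For a two-sample t-test with n per group and standardised effect d, the noncentrality is d × √(n/2) on 2n − 2 degrees of freedom. Power is the probability that the noncentral t falls outside the two-sided 5% limits.

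**Step 1: reproduce the plan's figure.** With d = 1 and n = 17, the noncentrality is √8.5 = 2.92 on 32 degrees of freedom, and power is 80.7%. With n = 16 it is 78.1%, so 17 is the smallest number per group that reaches 80%. The article does not label the 17 as per group, but the other readings do not fit:

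- 17 in total: about 49% power at d = 1.
- One-sided two-sample test at d = 1: 14 per group.
- Paired test: 10 patients at d = 1, or 14 at d = 0.83.

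Also, 17/0.85 = 20, which matches 20 per treatment and the 15% attrition allowed in the main sample size.

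**Step 2: standardise the cited effect.** d = 1.0/1.2 = 0.833.

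**Step 3: power at the cited effect**

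| Evaluable per group | Noncentrality at d = 0.833 | Power at d = 0.833 | Power at d = 1 |
|---|---|---|---|
| 17 | 0.833 × √8.5 = 2.43 | 65.4% | 80.7% |
| 20 | 0.833 × √10 = 2.64 | 72.8% | 86.9% |
| 24 | 0.833 × √12 = 2.89 | 80.7% | not needed |

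At d = 0.833, 24 is the smallest number of evaluable patients per group that reaches 80%. With the implied 15% dropout, 24/0.85 = 28.2, so 29 per group. The normal approximation gives slightly higher power (68.1% with 17, 75.0% with 20) and 23 per group for 80%, which leads to the same conclusion.

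**Step 4: effect detectable with 80% power.** With 17 per group it is d = 0.991, or 0.991 × 1.2 = 1.19 units. With 20 per group it is d = 0.909, or 0.909 × 1.2 = 1.09 units. Both exceed the cited 1.0.

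**Step 5: outcome.** The cited effect is for motility index. The listed manometry outcomes are HAPC number or frequency and percent time of cyclical retrograde contractions. The article gives no mean or SD for either.

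**The case against.** - **The stated power is true as written.** This stands. The article claims 80% for a standardised effect of 1, and that reproduces. A reader might infer that the stated 80% is itself a miscalculation, or is really 65%. The document does not support that: it never states a power for 0.83. What fails is the step from the cited result to the target.
- **65% is the low end.** This also stands. It applies if exactly 17 per group are evaluable; with all 20 it is about 73%. The range should be given, and the whole of it lies below 80%.
- **The nature of the SD is not stated.** True. The 1.2 could be a between-patient SD, the SD of a change or the SD of a within-patient difference. In a paired analysis, 17 patients at d = 0.83 would have about 90% power. But this trial compares changes between parallel groups, and a paired calculation does not yield 17. Baseline adjustment could also help, since the endpoint analysis adjusts for baseline where applicable. If 1.2 were an unadjusted endpoint SD, a baseline correlation of about 0.55 would raise 0.83 to 1 (0.833/√(1 − 0.55²) = 1.00), and about 0.40 would give 80% with 20 per group (0.833/√(1 − 0.40²) = 0.91). The article gives no such correlation, so this remains an assumption. It makes the 65% to 73% conditional, but it does not make 1.0 (1.2) equal to 1.
- **A standardised effect applies to any continuous outcome.** This is fair for roughly normal measures, so it would go too far to say that the plan has no power statement for HAPCs or retrograde time. What the citation cannot show is that an effect of 1 is plausible for them.

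**Conclusion.** The point holds as a mismatch between the cited effect and the target effect. The alosetron figures give a standardised effect of about 0.83, and the calculation uses 1. At 0.83, power is about 65% to 73% over the range from 17 to 20 evaluable per group, and 24 evaluable per group would be needed for 80%. This assumes that 17 means per group, that the test is a two-sided 5% two-sample t-test, and that 1.2 is the between-patient SD relevant to the comparison. If 1.2 is some other SD, those percentages change, but the citation as given still does not establish an effect of 1.

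Two further inferences should be resisted. A reader might conclude that this sub-study decides the retrograde brake hypothesis and that a null result would be over-read. The article only says that manometry will assess whether motor patterns change, and it plans regression comparisons between groups. A reader might also carry the problem over to the trial as a whole. The 400-patient calculation is separate and is not affected. This is a correction worth making to a mechanistic sub-study, no more.

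**What to change.** Keep 20 per group and restate the sentence, for example:

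> *For the effect cited for alosetron on motility index (1.0, SD 1.2; standardised 0.83), power is about 65% with 17 and 73% with 20 evaluable patients per group. Power of 80% holds for a standardised effect of about 0.99 (17 per group) or 0.91 (20 per group).*

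Say what kind of SD the 1.2 is, and label the 17 as per group. Add one sentence noting that the calculation is for motility index, while the listed manometry outcomes are HAPCs and percent time of cyclical retrograde contractions, so the cited effect does not show what effect size is plausible for those.

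The cost is wording only: no change to recruitment, procedures or analysis. The stated power becomes less favourable. Adding motility index as an outcome is optional, and the correction does not depend on it.

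### The cited manometry effect, 1.0 (SD 1.2), is a standardised effect of 0.83, so it does not support the effect of 1 on which the 80% power with 17 patients per arm rests.

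*Protocol article*

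**What the plan says.** Under Sample size, High-resolution left-sided colonic manometry, the protocol article cites the mean (SD) increase in motility index on alosetron compared with placebo and draws the power statement directly from it: "1.0 (1.2) [29], indicating we would have 80% power to detect a standardised effect size of 1 with 17 patients". The number is then raised: "We will aim for 20 patients on each treatment to allow for dropouts", which makes 40 patients, each studied twice.

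Three other places fix the setting of the calculation:
- General considerations: "All hypothesis tests will be two-sided with a 5% significance level".
- Trial design: "In total, 400 patients with IBS-D will be randomised 1:1 to receive either ondansetron or placebo", so the comparison is between parallel arms.
- Mechanistic studies: the manometry analysis is a linear regression on "The differences between treatment groups in changes in whole gut transit times, colonic motility measures" and the other mechanistic measures.

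**The concern.** A standardised effect is a mean difference divided by its SD. The sentence prints a mean and an SD and presents a standardised effect of 1 as what they indicate, but their ratio is 0.83. No other SD, rounding rule or clinical target is given to bridge the gap.

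The stake is how the sub-study will be read. Manometry is the planned test of the proposed increase in retrograde sigmoid motility (Potential mechanisms of action). A reader who takes the sentence at face value will believe that the study has 80% power for an effect as large as the one reported for alosetron. On the printed figures that is not shown. A null result could then be given more weight against the mechanism than the study can bear.

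**Working it through.** **Inputs.** Mean 1.0, SD 1.2, 80% power, standardised effect 1, 17 patients, 20 per treatment (manometry paragraph). Two-sided 5% (General considerations). Parallel arms, 1:1 (Trial design).

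**Method.** Two-sample t-test with n per arm, noncentrality d × √(n/2) and 2n − 2 degrees of freedom.

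**Step 1: reproduce the plan's figure.** For d = 1 and n = 17, the noncentrality is 1 × √8.5 = 2.92 and power is 80.7%. With 16 per arm it is 78.1%, so 17 is the smallest number per arm that reaches 80%. Other readings do not return 17:

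| Reading at d = 1 | Result |
|---|---|
| Two-sided t, per arm | 17 for 80% power |
| Two-sided normal approximation, per arm | 16 |
| One-sided normal approximation, per arm | 13 |
| Paired or one-sample t | 10 patients |
| 17 as the total of both arms | about 49% power |

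The per-arm reading also fits the next sentence. With the 15% attrition of the main calculation (assumed here, since the manometry paragraph gives no rate), 17/0.85 = 20 per treatment.

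**Step 2: standardise the cited effect.** 1.0/1.2 = 0.833.

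**Step 3: power for the cited effect, unadjusted.** This takes 1.2 as the SD of the between-arm comparison.

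| Analysed per arm | Noncentrality 0.833 × √(n/2) | Power |
|---|---|---|
| 17 | 2.43 | 65.4% |
| 20 | 2.64 | 72.8% |
| 23 | 2.83 | 78.9% |
| 24 | 2.89 | 80.7% |

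The normal approximation gives 68.1% at 17, 75.0% at 20, and 23 per arm for 80%. In the other direction, the smallest effect detectable with 80% power is 0.99 SD at 17 per arm and 0.91 SD at 20.

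**Step 4: allow for baseline adjustment.** Suppose 1.2 is a between-patient SD and the regression adjusts for the baseline study, with baseline/follow-up correlation ρ. The residual SD is 1.2 × √(1 − ρ²), so the effective d is 0.833/√(1 − ρ²). The article gives no ρ, so the values below are assumptions.

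| ρ | Effective d | Power at 17 | Power at 20 |
|---|---|---|---|
| 0.3 | 0.874 | about 70% | 77% |
| 0.4 | 0.909 | 73% | 80% |
| 0.5 | 0.962 | 78% | 84% |
| 0.55 | 0.998 | 81% | 87% |

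A change score without a baseline covariate would not gain in this way. Its SD is 1.2 × √(2(1 − ρ)), which equals 1.2 at ρ = 0.5 and is larger for any smaller ρ.

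**The case against.** The strongest reply is that the power statement is true as written. It claims 80% for an effect of 1, and 17 per arm delivers that. The article never claims 80% for 0.83. This stands, and it rules out the tempting reading that power is 65% instead of 80%: the two figures answer different questions. What remains is the link. The sentence offers 1.0 (1.2) as the ground for an effect of 1, and it is not.

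Second, the article does not say whether 1.2 is a between-patient SD, an SD of change or an SD of within-patient differences, and the cited source is not at hand. This also stands, so 65% is a conditional figure. A paired reading does not rescue the sentence, however. A paired test with d = 0.83 and 17 patients would have about 90% power, and a paired design needs 10 patients at d = 1 or 14 at d = 0.83 for 80%. None of these gives the stated combination, and this trial compares parallel arms.

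Third, each patient has a baseline study, and the Endpoint analysis section adjusts for baseline values where applicable. Adjustment could bring power close to or above 80%, as Step 4 shows. The article neither invokes this argument nor gives a correlation, so it widens the range without justifying an effect of 1.

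Fourth, the planned manometry measures are percent time of cyclical retrograde contractions and frequency of high-amplitude propagating contractions, not motility index. That is fair: the restated figure corrects the basis offered for the sample size and is not the power for those measures.

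A reader might also infer that the raw mean of 1.0 was taken for an already standardised value. Rounding, or a deliberate target of 1, fits the text equally well, and the document does not settle it.

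**Conclusion.** The point holds as a mismatch between the cited evidence and the effect size used. The cited figures give 0.83, and the article gives no reason for 1. The calculation for an effect of 1 is sound (80.7% at 17 per arm).

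For the cited effect, power is about 65% at 17 analysed per arm and 73% at 20 if 1.2 is the SD of an unadjusted between-arm comparison, and 24 per arm are needed for 80%. If 1.2 is a between-patient SD and baseline is adjusted for, with an assumed correlation of 0.3 to 0.5, power is about 70–78% at 17 and 77–84% at 20. The documents therefore do not support a flat statement that the sub-study is underpowered.

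The consequence is confined to an embedded sub-study of 40 of the 400 patients. The primary endpoint's sample size does not depend on it.

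**What to change.** Keep n = 40 and restate the sentence, for example:

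> The cited effect, 1.0 (SD 1.2), is a standardised effect of 0.83. Seventeen analysed patients per arm give 80% power only for effects of about 1.0 SD or more, and about 65% (20 per arm: 73%) for the cited effect without baseline adjustment, taking 1.2 as the between-patient SD.

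If the sponsor knows what the 1.2 refers to, or has a baseline/follow-up correlation, it should state these and give the adjusted figure instead. Alternatively, give a separate basis for choosing a standardised effect of 1 and stop attributing it to the cited result.

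The cost is one sentence and no extra patients. The stated power for the cited effect becomes less favourable.
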